### **Inclusion Criteria**

Women are considered eligible if they are pregnant and <24 weeks gestation; planning to continue their pregnancy; 21-45 years of age; enrolled in or eligible for Medicaid; speak English or, for women recruited in San Francisco, Spanish; and are contemplating sterilization after their delivery. By focusing on women <24 weeks gestation, we hope to capture women who are still deliberating about their post-partum contraception. If the woman is eligible, the Research Assistant reviews the informed consent and receives verbal or written consent from the woman to participate in the study.

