### **Screening**

For all sites, potential participants that contact the research team or are contacted by the research team either in-person or via phone, mail, email or text message will be given a pre-screening assessment consisting of several questions to ensure they meet basic study eligibility criteria. Written or verbal consent will be obtained to conduct the pre-screening questions. During the pre-screening assessment, interested participants will be given additional study details and an opportunity to ask questions and will also be asked about their access to technology for study participation. If the potential participant is interested in participating in the study, and meets pre-screening eligibility, they will be given the option to participate in the screening, consent, and initial study procedures (randomization, baseline assessment, intervention, and T1 assessment) either in-person or remotely via telephone and/or videoconference.

Due to the evolving nature of the COVID-19 pandemic, in person procedures and safety requirements may vary by site, depending on the current conditions in each region; local restrictions and regulations will be followed. For participants that choose to participate in the study in-person at Pittsburgh and ZSFG, a telephone appointment will be scheduled 24-48 hours before their scheduled in-person healthcare clinic visit. During this telephone appointment, a full study screening and COVID-19 screening will be conducted. If the potential participant meets full study eligibility criteria, and verbally screens negative for COVID-19 symptoms and risk factors, research staff will meet the participant before or after the participant's in-person healthcare appointment at their local study site (i.e., Magee Women's Hospital or [name] for Pittsburgh participants, and Zuckerberg San Francisco General Hospital for San Francisco participants) to complete the written informed consent for enrollment and the Baseline and T1 interviews.

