## Randomization

Randomization is stratified by site and occurs at the patient level to allocate participants to each of the 2 study arms in a 1:1 ratio, using permuted block randomization that is integrated into the web-based data collection system.

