## Sample Size Calculation

We based our sample size on the standardized mean differences (Cohen’s d) for the co-primary outcomes of knowledge (0.46) and decisional conflict (0.36) reported in the 2014 Cochrane review of decision aid RCTs. Assuming two-sided alpha levels of 0.025 (for each co-primary outcome) and 15% attrition, 175 women per arm afforded us 80% power to detect these differences.

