| In-person or virtual delivery of the Decision | [noted by research assistant at UT site, where virtual and in-person recruitment is being used]                   | BL | Dichotomous (in-person/virtual)                                                                                                                                                                                                                                                                                                                                                                                                                                                                                                                                                                                                                                                                                                                                                                                                                                                                                                                                     | Dichotomous (in-person/virtual)                                                                                                                                                                                                                                                                                        |

|                              |                                                                                                                                                                                                    |                         |                               |                               |
|------------------------------|----------------------------------------------------------------------------------------------------------------------------------------------------------------------------------------------------|-------------------------|-------------------------------|-------------------------------|
| Aid                          |                                                                                                                                                                                                    |                         |                               |                               |

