    - Provider sterilization counseling between T1 and T3 (composite variable of this question at T3 about counseling during this pregnancy isolating those who said they already received this counseling prior to or during this pregnancy at baseline)
    - Provider contraceptive counseling between T1 and T3
    - Medicaid consent signed between T1 and T3
    - Provider sterilization and/or Medicaid consent between T1 and T3

- **Subgroup Analyses (Interactions, no *a priori* hypothesis, not powered) of the Primary Outcomes by:**

*Regression model needs to control for site, including direct effects of the decision aid and the variable of interest below. Check for collinearity (VIF with a cut-off of 10)*

- Race/ethnicity (non-Hispanic Black, non-Hispanic White, Hispanic, non-Hispanic Other)
  - **Knowledge=decision aid + site + race/ethnciity + DA#Race/ethnicity**
  - **Decisional conflict= decision aid + site + race/ethnciity + DA#Race/ethnicity**
- Age (categorized for this analysis: <25, 25+)
  - **Knowledge= decision aid + site + age + DA#age**
- Completed Decision Aid in-person or virtual
- Recruitment Site (California, Pennsylvania, Tennessee)
- Language of the consent form (English vs Spanish)
- Education level (HS or less including GED vs. any post-high school or more)
- Provider counseling/consent form signed at T1
  - Provider sterilization counseling at baseline (before this pregnancy, during this pregnancy)

- **Participant Satisfaction with Current Contraceptive Method(s) at Time 3:** Compared to women who receive usual care alone, women randomized to the decision aid arm will report greater satisfaction with their current contraceptive method(s) at Time 3

- **Desire for sterilization:** variable will be used to assess baseline differences (pre-decision aid for intervention group, T1 for control), changes from baseline to T1 for intervention groups, and differences between post-decision aid for intervention group vs T1 for control group.

- To test exploratory hypotheses, we will first use linear regression (using the continuous measure 1-5 where higher score indicates higher desire for sterilization) to test intervention effects (pre-intervention baseline vs post-intervention T1; post-intervention vs T1 control), controlling for study site.

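### The subgroup interaction by mode of decision-aid completion cannot be estimated as written, because controls have no value for the modifier; the language interaction can be, but needs an arm-by-site term

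*Combined protocol and SAP*

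**What the plan says.** The combined protocol and SAP, under Exploratory Hypotheses, sets out subgroup analyses of the two co-primary outcomes. It states that they carry no prior hypothesis and no power. One model form serves every modifier: arm, site, modifier and arm-by-modifier. The worked examples for race/ethnicity and age carry site as a main effect only. The only diagnostic is a variance inflation factor (VIF) with a cut-off of 10. The modifiers include "Completed Decision Aid in-person or virtual" and "Language of the consent form (English vs Spanish"). Recruitment site is listed as a separate modifier.

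**Mode.** The Covariates and Baseline Characteristics table defines the variable as delivery of the aid, gives its time point as baseline, and describes it as "noted by research assistant at UT site, where virtual and in-person recruitment is being used". The Screening section says of women at all sites who pass pre-screening that "they will be given the option to participate in the screening, consent, and initial study procedures" either in person or remotely, and it describes in-person study visits at Pittsburgh and San Francisco. Under Intervention and Timepoints, the intervention arm uses the aid after randomisation, while controls go straight to the T1 assessment, in person or by phone.

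**Language.** The Inclusion Criteria admit English speakers and, "for women recruited in San Francisco, Spanish" speakers. The synopsis gives no site limit on Spanish. The covariate table holds the language of the aid, deduced from which aid fields were completed, and not the language of the consent form.

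**The concern.** An interaction asks whether the arm difference changes across levels of a modifier, so each level needs women from both arms. A variable that describes how the aid was used has no level for a woman who never used it. An analyst following the plan literally would find that the model cannot be fitted, or would settle on a coding under which the term labelled arm-by-mode is really a comparison of aid users who chose one mode with aid users who chose the other. Reported as effect modification, that would mislead a reader interested in remote delivery.

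The language term raises a different and weaker question. Every Spanish speaker comes from one site, and the model does not let the aid's effect vary by site. A site difference in the aid's effect could therefore be read as a language difference.

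**Working it through.** **1. The plan's own figure.** No figure is given for the subgroup analyses. The sample size statement reads "Assuming two-sided alpha levels of 0.025 (for each co-primary outcome) and 15% attrition, 175 women per arm afforded us 80% power", with effect sizes for the "co-primary outcomes of knowledge (0.46) and decisional conflict (0.36"). For the smaller effect, n per arm = 2(z₀.₉₈₇₅ + z₀.₈₀)²/d² = 2(2.241 + 0.842)²/0.36² = 146.7, so 147. Allowing for attrition, 147/0.85 = 172.9, so 173, against the stated 175. With 175 × 0.85 = 148.75 per arm, power is 80.6% at d = 0.36 and 95.8% at d = 0.46. The figure reproduces, and nothing below alters it.

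**2. Inputs for the subgroup models.** From the documents: 350 women; randomisation stratified by site to "allocate participants to each of the 2 study arms in a 1:1 ratio"; the model form above; Spanish only at San Francisco. Assumed, because the documents do not say: sites of 117, 117 and 116; a Spanish share at San Francisco of 20% to 80%; all 350 women analysed.

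**3. Mode.** The model has six columns: intercept, arm, two site indicators, mode, arm × mode.

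- *Controls missing.* About 175 aid-arm women remain. Arm equals the intercept and arm × mode equals mode. Rank is 4 of 6, so neither the arm effect nor the interaction exists.
- *Controls coded to one level.* With that level as reference, arm × mode equals mode. Rank is 5 of 6. The one surviving coefficient is in-person versus virtual within the aid arm.
- *Session mode recorded in both arms.* Rank is 6 of 6 and the interaction is estimable. This holds even if mode varies only at the Tennessee site.

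**4. Language.** Using consent-form language, which exists in both arms, rank is 6 of 6 as long as San Francisco also enrols English speakers. Suppose language has no effect on the arm difference, but the aid's effect at San Francisco differs from that elsewhere by δ. Spanish speakers all carry δ, while English speakers carry it only in proportion to their share at San Francisco. So

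bias in arm-by-language = δ × (1 − share of English speakers who are at San Francisco).

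| Spanish share at San Francisco | English speakers at San Francisco / all English speakers | Bias | SE as planned | SE with arm-by-site |
|---|---|---|---|---|
| 20% | 92/326 = 0.28 | 0.72 δ | 0.42 SD | 0.46 SD |
| 50% | 58/292 = 0.20 | 0.80 δ | 0.29 SD | 0.37 SD |
| 80% | 24/258 = 0.09 | 0.91 δ | 0.24 SD | 0.46 SD |

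As an illustration with an assumed δ of 5 points and the middle row, the false interaction is 5 × 0.80 = 4 points. If δ = 0, the bias is zero. The largest VIF over these shares is 4.56, so the cut-off of 10 would not flag the problem. With arm-by-site added, rank is 8 of 8 and the bias is 0. Language and site become inseparable (rank 5 of 6) only if every San Francisco participant were a Spanish speaker.

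**The case against.** The best defence on mode is that the fault lies in the label. Women choose in-person or remote participation for the whole initial session before consent and randomisation, controls also have a visit mode, and the covariate table dates the variable to baseline, which precedes randomisation. The design therefore contains a usable modifier for both arms. That stands as a reason why the repair is easy. It does not rescue the text: the variable is named and defined as delivery of the aid, no session-mode variable is listed, and recording is described for one site only. That restriction is explained by how women are *recruited* in Tennessee, whereas the Screening section lets women elsewhere *participate* in person.

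It is also fair that session mode is self-selected, so even a correctly fitted interaction is an association and not a causal effect of mode.

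On language, a reader might infer that nesting in one site makes that interaction invalid too. The documents do not support this. Consent-form language is known for both arms, English speakers are eligible at San Francisco, and the term is estimable. Bias needs a site difference in the aid's effect, for which the documents give no evidence. The planned site subgroup would display such a difference, although a separate model does not remove it from the language estimate.

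Finally, these analyses are declared exploratory and unpowered. That limits the severity, but a warning about low power covers imprecision and not an undefined term.

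**Conclusion.** The mode interaction is wrong as written: it is either not estimable or becomes a non-randomised contrast within the aid arm. This follows from the definitions alone and needs no numerical assumption.

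The language point is conditional and secondary. The interaction would absorb about 0.72 to 0.91 of any San Francisco-specific aid effect, assuming equal sites and Spanish shares of 20% to 80% there, and none if the aid works equally across sites. It also depends on using consent-form language: the aid-derived variable in the covariate table has no value in controls and would repeat the mode problem.

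Two further inferences should be resisted. Nothing here touches the co-primary analyses, their alpha or the sample size. Nor do the documents say that the mode result will guide how the aid is delivered. Severity is low.

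**What to change.** **Mode.** Redefine the modifier as the mode of the initial session (in-person or remote), fixed before randomisation and recorded for every woman in both arms at all sites. Fit arm by session mode, and state that mode is self-selected and the interaction is an association. If control mode cannot be recovered, delete the interaction and describe aid-arm outcomes by mode, labelled non-randomised. The cost is SAP wording and one database field, or a back-fill if suitable session records exist; the documents do not describe any.

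**Language.** Name consent-form language as the analysis variable and add it to the covariate table. Add arm-by-site to that model, or report the estimate within San Francisco only. Reconcile the synopsis with the Inclusion Criteria on where Spanish speakers are eligible. The cost is precision: the standard error is about 0.37 to 0.46 SD, against 0.24 to 0.42 SD without the extra term. Even at 0.37, the plan's 97.5% interval would have a half-width of about 2.24 × 0.37 = 0.83 SD, so the result should be reported as descriptive.

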| Language of the decision aid                                                                                                                                                                                                                      | X  |    |    |    |

Notes: \*this was measured before and after the decision aid for intervention group at at the very beginning of T1 assessment for control group; \*\*this was only measured for the intervention group

409

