### Primary and Secondary Hypotheses

For the following primary and secondary hypotheses, we will conduct an intention-to-treat analysis using linear or logistic regression to test intervention effects controlling for study site. The beta coefficient and corresponding 97.5% confidence interval will be used to assess the effect of the intervention.

- **Primary Hypothesis a:** Compared to women who receive usual care alone, women randomized to the decision aid arm will have greater knowledge about sterilization and alternative options at T1
- **Primary Hypothesis b:** Compared to women who receive usual care alone, women randomized to the decision aid arm will have lower decisional conflict in postpartum contraceptive choice at T1
- **Secondary Hypothesis a:** Compared to women who receive usual care alone, women randomized to the decision aid arm will also be less likely to select sterilization and more likely to select an alternative method at T1
- **Secondary Hypothesis b:** Compared to women who receive usual care alone, women randomized to the decision aid arm will also be more satisfied with their decision at 3-month follow-up (T3)

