- We will also use ordinal regression (using the recoded 3, 4, and 5 values where higher score indicates higher strength of desire but not for/against sterilization) to test intervention effects controlling for study site.

- **Participant Knowledge about Tubal Sterilization at Time 2:** Compared to women who receive usual care alone, women randomized to the decision aid arm will have greater knowledge about sterilization and alternative options at T2.

- ***Sensitivity Analyses:*** We will run sensitivity analyses to test robustness of the intervention effects after adjusting for differences in:
  - Provider sterilization counseling between T1 and T2 (“since our last meeting”)
  - Provider contraceptive counseling between T1 and T2 (“since our last meeting”)
  - Medicaid consent signed between T1 and T2 (“since our last meeting”)
  - Provider sterilization and/or Medicaid consent signed between T1 and T2 (“since our last meeting”)
- **Participant Decisional Conflict in Postpartum Contraceptive Choice at Time 2:** Compared to women who receive usual care alone, women randomized to the decision aid arm will have lower decisional conflict in postpartum contraceptive choice at Time 2
- ***Sensitivity Analyses:*** We will run sensitivity analyses to test robustness of the intervention effects after adjusting for differences in:
  - Provider sterilization counseling between T1 and T2 (“since our last meeting”)
  - Provider contraceptive counseling between T1 and T2 (“since our last meeting”)
  - Medicaid consent signed between T1 and T2 (“since our last meeting”)
  - Provider sterilization and/or Medicaid consent signed between T1 and T2 (“since our last meeting”)
- **Contraceptive Method Selected at Time 2:** Compared to women who receive usual care alone, women randomized to the decision aid arm will be less likely to select sterilization at T2 and more likely to select an alternative method
- **Contraceptive Method(s) Used at Time 3:** Compared to women who receive usual care alone, women randomized to the decision aid arm will be less likely to select sterilization at T3 and more likely to select an alternative method
- **Ease in Contraceptive Decision Making at Time 1:** Compared to women who receive usual care alone, women randomized to the decision aid arm will report greater ease in contraceptive decision making at Time 1

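### The pre/post desire regression has no term for pairing within woman, and pre-exposure desire can inform the method-selected analysis only if the arms happen to differ on it

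*Combined protocol and SAP*

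**What the plan says.** The note under the Variables table says of desire that "this was measured before and after the decision aid for intervention group"; controls answer once, at the start of T1. The Exploratory Outcome Measures table lists two uses: pre-post change in the intervention arm, and post-aid intervention versus T1 control.

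For both contrasts, Exploratory Hypotheses names linear regression on the 1-5 score "to test intervention effects (pre-intervention baseline vs post-intervention T1; post-intervention vs T1 control), controlling for study site". An ordinal regression on a score folded to 3, 4 and 5 follows, again "to test intervention effects controlling for study site", without saying which contrast it tests. The opening of that section bases inference on the beta coefficient and its 97.5% interval.

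For method selected at T1, a secondary outcome, Primary and Secondary Hypotheses plans an intention-to-treat analysis "using linear or logistic regression to test intervention effects controlling for study site". Desire also appears under Covariates and Baseline Characteristics, where the pre-aid score (intervention) and the T1 score (control) are to be compared between arms. A sensitivity analysis for the primary and secondary outcomes adjusts for baseline characteristics that differ significantly between arms and are also associated with the outcome.

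**The concern.** The pre/post contrast is made within women, but its model carries site and nothing that links a woman's two answers. Followed as written, it gives a standard error that ignores their correlation, so a real shift in desire after the aid could go undetected.

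The second issue is efficiency. Desire on a 1-5 scale is the nearest thing in the data to a baseline value of choosing sterilization. The covariate rule admits it only if the arms differ significantly, and under randomization such differences arise by chance. If the unstated threshold is 0.05, that is about one trial in 20. The precision gained from a covariate depends on how well it predicts the outcome, not on whether the arms happen to differ on it, so a strongly prognostic desire score would usually be left out.

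**Working it through.** **The plan's own figure.** The documents give no figure for desire or for method selected; their only one is the sample size. It rests on "two-sided alpha levels of 0.025 (for each co-primary outcome) and 15% attrition", with the smaller effect being d = 0.36. Per arm, n = 2(2.241 + 0.842)² / 0.36² = 146.7, so 147, and 147/0.85 = 172.9, so 173. With the noncentral t, n = 148 and 148/0.85 = 174.1, so 175. This reproduces the stated size. It matters here only because it supplies n = 175 per arm. Attrition is not applied below, because desire and method selected at T1 are collected at the initial study contact.

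**Pre/post desire.** The within-woman correlation rho and the SD are not in the documents and are assumed. Variances are taken as equal and site is ignored. In SD units:

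- SE, two answers treated as independent: sqrt(2/175) = 0.107
- SE, paired: sqrt(2(1 - rho)/175)
- Ratio: 1/sqrt(1 - rho)
- Actual type I error of the unpaired test at nominal 0.025: 2[1 - Φ(2.241 × ratio)]
- Power for an assumed change of 0.2 SD: paired, Φ(0.2/SE_paired - 2.241); unpaired, Φ((0.2 - 2.241 × 0.107)/SE_paired)

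| rho (assumed) | Paired SE | Ratio | Actual type I error | Power, unpaired | Power, paired |
|---|---|---|---|---|---|
| 0.3 | 0.089 | 1.20 | 0.0074 | 33% | 50% |
| 0.5 | 0.076 | 1.41 | 0.0015 | 30% | 66% |
| 0.7 | 0.059 | 1.83 | 0.00004 | 25% | 88% |
| 0.9 | 0.034 | 3.16 | about 0 | 12% | about 100% |

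For any positive rho the error is conservative.

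**Method selected at T1.** Logistic regression was simulated with site in the model, with and without desire, at two-sided 0.025 and 800 runs per setting. All of the following are assumed: 60% of controls and 45% of the intervention arm choose sterilization; desire scores 1 to 5 have frequencies 5, 10, 25, 30 and 30%; the three sites are equally likely and have no effect of their own. The marginal rates are held fixed while the strength of desire varies.

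| Log-odds slope per desire point | Power, site only | Power, site + desire | Gain (points) | Conditional log OR |
|---|---|---|---|---|
| 0 | 71% | 71% | 0 | -0.61 |
| 0.5 | 73% | 75% | 2 | -0.65 |
| 1.0 | 69% | 81% | 12 | -0.78 |
| 1.5 | 70% | 86% | 16 | -0.95 |

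The Monte Carlo SE of one power near 70% is sqrt(0.7 × 0.3/800) = 1.6 points. With no true effect, rejection was 1.9% to 2.5% across both models.

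The last column shows why the effect measure must be named. The risk difference is 15 points in every row and the marginal odds ratio is (0.45/0.55)/(0.60/0.40) = 0.55. The desire-adjusted odds ratio nevertheless moves from 0.55 to exp(-0.95) = 0.39.

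**The case against.** A reader might infer that the plan treats a woman's two answers as independent. It never says so. It speaks of changes from baseline to T1 and of pre-post changes, and regressing each woman's change on site would fit those words. This stands as a limit on the claim. The rest of the wording fits a change score less well: the outcome named is the 1-5 score, one sentence gives the same model to the within-woman and the between-arm contrast, and inference rests on a beta coefficient, whereas a one-arm change-score model gives the mean change through its intercept or a marginal mean. A reader might also attach the ordinal model to the pre/post contrast, but the plan does not say that it is used there.

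On method selected, a reader might infer that the site-only model is faulty or that desire has been excluded. Neither holds. Adjusting for site, the stratification factor, gives a valid randomized test, and leaving out a prognostic covariate neither biases it nor inflates type I error. Desire has a route in, though a conditional one.

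The strongest objection to making desire part of the main model is timing. Randomization precedes both the aid and T1, so desire is asked after allocation in both arms, and nothing shows that the woman or the interviewer was unaware of allocation when it was asked. That is reason enough to keep the site-only model as the main analysis. The gain may also be modest: only women contemplating sterilization are enrolled, which could narrow the range of desire.

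**Conclusion.** Both parts hold in limited form.

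The pre/post analysis leaves the handling of paired answers unspecified and, read literally, is unpaired. If fitted that way, the cost is a standard error 1.2 to 3.2 times too large for assumed rho 0.3 to 0.9: a loss of precision and power in one exploratory, single-arm contrast. With or without pairing, that contrast is a change in one arm and not a randomized intervention effect.

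The model for method selected is valid but leaves usable information to a rule triggered by chance imbalance. The gain forgone is 0 to about 16 points of power under the assumed rates, and nil if desire does not predict the choice. The documents give no rho, SD, sterilization rate or desire-outcome association, so every size here is conditional on those assumptions.

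**What to change.** 1. State that pre/post desire is analysed within woman: either a change-score model with site, reporting the mean change averaged over sites and its 97.5% interval, or a mixed model or GEE with a participant term. If the ordinal model is meant for this contrast, give it the same treatment; if not, name the contrast it tests. Describe the result as a one-arm change.
2. Keep the site-only logistic model as the main analysis of method selected at T1. Beside it, prespecify an analysis adjusted for site and pre-exposure desire (1-5), to be run whatever imbalance is seen. Report a standardized risk difference, and label any odds ratio as conditional or marginal.
3. State that desire is asked after allocation, so it is pre-exposure but not pre-randomization. State also that it cannot serve as a covariate in the post-aid versus control comparison of desire itself, because controls have a single score.

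The cost is a few lines of SAP text and one extra model. No new data are needed, and the sample size and the co-primary analyses do not change.
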